## Abstract

**Background:**

Long-term outcomes of lung transplantation are severely affected by comorbidities and development of chronic rejection. Among the comorbidities, kidney insufficiency is one of the most frequent and it is mainly caused by the cumulative effect of calcineurin inhibitors (CNIs). Currently, the most used immunosuppression protocols worldwide include induction therapy and a triple-drug maintenance immunosuppression, with one calcineurin inhibitor, one anti-proliferative drug, and steroids. Our center has pioneered the use of alemtuzumab as induction therapy, showing promising results in terms of short- and long-term outcomes. The use of alemtuzumab followed by a low-dose double drug maintenance immunosuppression, in fact, led to better kidney function along with excellent results in terms of acute rejection, chronic lung allograft dysfunction, and survival (Benazzo et al., PLoS One 14(1):e0210443, 2019). The hypothesis driving the proposed clinical trial is that de novo introduction of low-dose everolimus early after transplantation could further improve kidney function via a further reduction of tacrolimus. Based on evidences from kidney transplantation, moreover, alemtuzumab induction therapy followed by a low-dose everolimus and low-dose tacrolimus may have a permissive action on regulatory immune cells thus stimulating allograft acceptance.

**Methods:**

A randomized prospective clinical trial has been set up to answer the research hypothesis. One hundred ten patients will be randomized in two groups. Treatment group will receive the new maintenance immunosuppression protocol based on low-dose tacrolimus and low-dose everolimus and the control group will receive our standard immunosuppression protocol. Both groups will receive alemtuzumab induction therapy. The primary endpoint of the study is to analyze the effect of the new low-dose immunosuppression protocol on kidney function in terms of eGFR change. The study will have a duration of 24 months from the time of randomization. Immunomodulatory status of the patients will be assessed with flow cytometry and gene expression analysis.

**Discussion:**

For the first time in the field of lung transplantation, this trial proposes the combined use of significantly reduced tacrolimus and everolimus after alemtuzumab induction. The new protocol may have a twofold advantage: (1) further reduction of nephrotoxic tacrolimus and (2) permissive influence on regulatory cells development with further reduction of rejection episodes.

**Trial registration:**

EUDRACT Nr 2018-001680-24. Registered on 15 May 2018

## Administrative information

Note: the numbers in curly brackets in this protocol refer to SPIRIT checklist item numbers. The order of the items has been modified to group similar items (see http://www.equator-network.org/reporting-guidelines/spirit-2013-statement-defining-standard-protocol-items-for-clinical-trials/).

## Introduction

### Background and rationale {6a}

Lung transplantation is an established therapy for end-stage lung diseases; however, long-term outcomes are severely affected by comorbidities and by the development of chronic rejection. Kidney insufficiency is the comorbidity most frequently recorded after lung transplantation with an incidence of 50% at 5 years and 70% at 10 years. It is mainly caused by the cumulative nephrotoxic effect of calcineurin inhibitors (CNIs). Moreover, chronic rejection (chronic lung allograft dysfunction—CLAD) hampers long-term outcomes and poses a big financial burden. During the last years, significant efforts have been made to improve kidney function and reduce the occurrence of CLAD. With this purpose, different immunosuppression strategies have been developed. Currently, the most commonly used protocols include induction therapy and a triple-drug maintenance immunosuppression, with a CNI (mainly tacrolimus), an anti-proliferative drug (mainly MMF), and steroids.

#### Immunosuppression

##### Induction immunosuppression

The rationale underlying induction immunosuppression is twofold: (1) to reduce the dose of maintenance immunosuppression, thereby minimizing its adverse effects, and (2) to reduce the incidence of ACR, which is a known risk factor of CLAD. According to the 33rd report from the Registry of the ISHLT, approximately 50% of patients transplanted in the past 10 years received some type of induction therapy [1]. Currently, the majority of lung transplant centers use IL2R Antagonists (mainly basiliximab) with contrasting outcomes [2–6]. Basiliximab blocks the IL-2 binding site of CD25, inhibiting effector T cells and other proinflammatory cells. Polyclonal anti-lymphocyte preparations (ATG) are the second most used induction therapy. ATG-mediated mechanisms include apoptosis and anergy of T cells, antibody-dependent cellular cytotoxicity (ADCC), and complement-mediated lymphocyte lysis [7–9]. More recently, an increasing number of centers started using alemtuzumab, a humanized monoclonal antibody targeting CD52, as induction therapy. The receptor recognized by this antibody is expressed on several immune cells (T and B lymphocytes, natural killer (NK) cells and macrophages), and its activation induces cell lysis leading to immune cell depletion [10, 11]. B cell counts recover 3 to 6 months and T cell counts in 12 to 24 months after treatment [10, 12]. Few studies investigated the specific reconstitution of T and B cell compartment. In the T cell compartment, CD4^+^CD45RO^+^ effectory memory T cells preferentially reconstitute 12 to 24 months after depletion, constituting the predominant T cell subset [12–17]. According to Bouvy and colleagues, in fact, CD4^+^CD45RO^+^ T cells seem to be resistant to alemtuzumab-driven depletion and moreover, to some extent, CD4^+^CD45RA^+^ näive T cells may convert to a memory phenotype in a lymphopenic environment [15]. In parallel to the increase of the effector memory T cells, frequency of CD4^+^CD25^+^FoxP3^+^ Treg cells seems to increase after the first month after alemtuzumab depletion [15]. Clinical data are supportive for the expansion of Tregs in organ transplant recipients after treatment with alemtuzumab [18]. In kidney transplant recipients, Bloom et al. reported an increase of Tregs and of the ratio of Treg/Teff compared to the pre-transplant baseline [16]. This could not be found in patients after basiliximab induction [16]. Similarly, Noris and colleagues showed an increase of CD4^+^CD25^+^FoxP3^+^ Tregs in kidney transplant recipient treated with alemtuzumab and sirolimus up to 24 months after depletion therapy [12]. The same set of cells showed a hyporesponsive phenotype against alloantigens [12]. A similar reconstitution pattern was also found in the field of multiple sclerosis, where alemtuzumab is an established therapeutic agent for relapsing-remitting forms. In addition to a predominant CD4CD45^+^RO^+^ and CD4^+^CD25^+^FoxP3^+^ T cells, a clear increase of anti-inflammatory cytokines and a suppression of Th1 and Th17 transcription factors as well as pro-inflammatory cytokines was observed [13, 14]. In summary, it seems that alemtuzumab therapy is associated with higher levels of memory T cells and Tregs. Whether this phenomenon is due to a selective depletion or proliferation is still unclear. After reconstitution, the B cell compartment mainly consists of IgM-producing näive B cells and transient B cells [10, 12]. Such phenotypic changes in B cells play a crucial role in allograft tolerance mechanisms [19]. In stable immunosuppression-free kidney recipients, a higher percentage of this subset of B cells was found. Based on these findings it is tempting to speculate whether alemtuzumab induction therapy creates an immunological environment with regulatory characteristics. To date, published data on the use of alemtuzumab in lung transplantation are scarce. One of the biggest series was published in 2011 by Shyu and colleagues. In their 5-year experience, the alemtuzumab group showed improved patient and graft survival compared to the non-induction and daclizumab group. Moreover, freedom from ACR, lymphocytic bronchiolitis (LB), and bronchiolitis obliterans (BO) was improved [20]. Furuya and colleagues reviewed the UNOS database and identified 738 patients receiving alemtuzumab induction therapy [21]. These patients had a significant better survival and showed a lower risk for CLAD.

##### Maintenance immunosuppression

The current maintenance immunosuppressive protocols are calcineurin inhibitor-based “triple-drug” regimens [1], based on the combination of CNI, anti-proliferative agents and steroids.

CNIs are the main immunosuppressive agents used in lung transplantation. They are nephrotoxic, neurotoxic, and associated with other side effects [22, 23]. CNIs target the intracellular phosphatase calcineurin, which inhibits the nuclear translocation of the cytosolic nuclear factor of activated T cells (NFAT). NFAT activates IL-2 transcription, which regulates proliferation and maturation for all T cell subtypes, including Tregs [24]. The effects of CNIs on Tregs have been shown to be dose and duration dependent. High-dose but not low-dose CNI alters gene expression in Tregs [25]. Moreover, NFAT partly resides into the nucleus of Tregs, making them resistant to low-dose action of CNI [26–28]. Current clinical trials in the field of kidney transplantation evaluate the efficacy and safety of CNI-sparing protocols to reduce nephrotoxicity. The observation that Tregs are resistant to low-dose CNI and that the combination of CNI with mTOR inhibitors restores Tregs [25–28] suggest that whenever feasible the reduction of CNI could not only improve kidney function but also support Tregs development.

Sirolimus and everolimus are two newer anti-proliferative agents of the mTOR inhibitor class. Their role in lung transplantation, however, is still debated. Everolimus allows to efficiently maintain a stable systemic immunosuppression level in combination with lower tacrolimus dosage [29–33]. As a consequence, everolimus is usually introduced in the long-term follow-up to stop further deterioration of kidney function. The potential of this agent to prevent CLAD, however, is still matter of debate and contrasting results have been published. Nowadays, mTOR inhibitors are mainly used to reduce the dose of CNI, when kidney dysfunction starts to deteriorate. In addition, there is evidence showing that everolimus favors Tregs development over Tconvs [34–38]. This effect is dose-dependent and high doses of mTOR inhibitors may negatively influence Tregs function [39]. In kidney transplant recipients, for example, patients on sirolimus show a 4-fold increase in circulating Tregs when compared to patients receiving cyclosporine [40]. Moreover, a conversion from a CNI-based to a rapamycin-based regimen led to an increase of peripheral Tregs in kidney and liver recipients [41, 42]. This effect is dose-dependent and high doses of mTOR inhibitors may negatively influence Tregs function [39]. Crucial nodes for the development and homeostasis of Tregs are TCR and IL-2R engagement as well as the PI3K-Akt-mTOR signaling pathway [38]. Low-dose CNI may not harm Tregs by deprivation of IL-2 [26] while concomitantly may inhibit intranuclear translocation of cytoplasmatic NFAT in Teffs. Low-dose mTOR inhibition may mediate the transcription of Tregs-specific genes through the activation of Forkhead box O (Foxo) transcription factors and inhibition of mTORC1 and 2 [38]. Thus, a combined CNI and mTOR inhibition could drive reprogramming of gene expression towards a pro-tolerogenic signature.

## Objectives {7}

According to our preliminary experience, the use of alemtuzumab induction and the consequent reduction of CNI is associated with an improvement of glomerular filtration rate. However, long-term kidney function is still impaired by the steady cumulative kidney damage driven by tacrolimus. In parallel, despite excellent freedom from acute rejection, chronic rejection rate is still high with approximately 25% of patients at 5 years [43]. This trial proposes a new immunosuppression protocol based on the early administration of low-dose everolimus in the attempt of preventing CNI-driven kidney damage and stimulating allograft tolerance. The addition of de novo everolimus early after transplantation, in fact, has two potential advantages: (1) it allows a significant reduction of nephrotoxic tacrolimus and (2) together with alemtuzumab it could have a permissive influence on regulatory cells development with reduction of chronic rejection rate.

Our primary objective is to analyze the effect of the proposed low-dose immunosuppression protocol on kidney function. As secondary objectives we intend to assess the difference between the investigational and the control immunosuppression protocol in terms of freedom from ACR, AMR, and CLAD, overall survival, occurrence of de novo donor-specific antibodies (DSA), occurrence of CMV infections, and occurrence of other comorbidities (e.g., hypertension, dyslipidemia, diabetes, tremor). As experimental objectives, immunomodulatory cell subsets will be characterized overtime and gene expression will be profiled in both groups, to gain insight into the potential immunomodulatory mechanisms of the proposed low-dose immunosuppression.

## Trial design {8}

This trial is a non-blinded randomized prospective trial. Since the dose of immunosuppressive agents will be adapted to reach the blood trough levels, a blinding is not realistically possible. One hundred ten patients respecting the inclusion criteria and exclusion criteria will be randomized into two groups at postoperative day 30. In case of incomplete healing of bronchial anastomosis, patients will be reevaluated for inclusion between postoperative day 30 and 60. Each group will include 55 patients. Patients will be stratified according to glomerular filtration rate (GFR) values before randomization (≥ 40–60 ml/min/1.73m^2^, > 60–75 ml/min/1.73m^2^, or > 75–100 ml/min/1.73m^2^) and CMV status (low risk vs high risk). Such stratification will ensure to equally allocate patients at high risk of kidney dysfunction in the two groups.

## Methods: participants, interventions, and outcomes

### Study setting {9}

Medical University of Vienna, Department of Surgery, Division of Thoracic Surgery, Head: [name]

### Eligibility criteria {10}

Inclusion criteria:
Bilateral lung transplantationAge > 18 yearsComplete healing of bronchial anastomosis

Exclusion criteria:
Inclusion in other studiesPre-transplant colonization with Burkholderia or resistant Mycobacterium abscessusWound infection at randomization

### Additional consent provisions for collection and use of participant data and biological specimens {26b}

Based on the guidelines of the ethical review committee, participants are asked to give consent for participation to trial, for collection and use of blood samples for scientific investigations and for dissemination of the results undersigning a single informed consent. The participants are not allowed to give limited consent.

## Interventions

### Explanation for the choice of comparators {6b}

The trial will compare a new maintenance immunosuppression protocol based on low-dose CNI and mTOR inhibitors with our standard of care, namely a maintenance immunosuppression based on CNI and steroid. The investigational medical products are tacrolimus (CNI) and everolimus (mTOR inhibitor).

### Intervention description {11a}

After transplantation, alemtuzumab will be given as a single dose of 30 mg on the intensive care unit (ICU). All included patients will receive maintenance immunosuppression protocol until randomization according to Table 1. After randomization, patients will be treated according to the protocol to the summarized in Table 2. According to current evidence, B cells reconstitute between 6 to 12 months after alemtuzumab induction. As a consequence, mycophenolate mofetil, an immunosuppressive agent also targeting B cells, will be introduced after 12 months to prevent incidence of acute humoral rejection.

**Table 1 Tab1:** Immunosuppression protocol during the first month after LuTx is the same in the two groups

*Time after LuTx*	Tacrolimus trough blood level (ng/ml)	Aprednisolone (mg/kg)
1–2 months	8–10	0.2

**Table 2 Tab2:** Immunosuppression protocol after randomization. In the treatment group, patients will receive a reduced dose of everolimus and tacrolimus whereas control patients will receive our standard immunosuppression. MMF will be introduced in both groups 12 months after transplantation

*Time after LuTx*	Tacrolimus trough blood level (ng/ml)		Everolimus trough blood level (ng/ml)		Aprednisolone (mg/kg)	MMF
	Control	Treatment	Control	Treatment	All patients	All patients
1–3 months	8–10	4–5	–	4–5	0.2	–
3–6 months	6–8	3–4	–	3–4	0.15	–
6–12 months	6–8	3–4	–	3–4	0.1	–
12–24 months	5–7	2.5	–	2.5	5 mg/d	1–1.5 g 2× a day

Perioperative infectious prophylaxis will be based on broad-spectrum antibiotics or adapted to resistance testing. All patients will receive a lifelong *Pneumocystis* prophylaxis with trimethoprim-sulfamethoxazole. Prophylactic inhalation therapy with amphotericin B and refobacin will be provided for 1–3 months. CMV prophylaxis will include CMV hyperimmunoglobulines (POD 1, 7, 14, and 21) together with valganciclovir for a minimum of 3 months. In high-risk patients (donor CMV IgG positive, recipient CMV IgG negative), a 12-month prophylaxis will be performed. Follow-up visits and pulmonary function test will take place once a month during the first year and later every 3 months. Bronchoscopy with transbronchial biopsy (TBB) and bronchoalveolar lavage (BAL) will be performed 1, 2, 3, 6, 12, 24 months after transplantation. A chest computed tomography (CT) will be done once a year. Biopsies will be classified according to ISHLT criteria [44]. ACR grade A2 and LB B2 or higher will be primarily treated with steroids for 3 days with consecutive dose tapering, and in case of non-response, ATG (2 mg/kg) will be administered for 5 days, followed by extracorporeal photopheresis (ECP) if necessary. Kidney insufficiency will be defined as GFR < 60 mL/min/1.73 m^2^ for ≥ 3 months. Infectious complications, including *Aspergillus* infection, will be defined as presence of pathogens with clinical signs and symptoms and need for specific treatment. Donor-specific antibodies (DSA) testing will be performed at each follow-up visit. AMR will be defined according to the ISHLT consensus. Patients with clinical AMR will be firstly treated by plasmapheresis followed by ECP.

### Criteria for discontinuing or modifying allocated interventions {11b}

The investigator must temporarily interrupt or permanently discontinue the study drug if continued administration of the study drug is believed to be contrary to the best interests of the patient. The interruption or premature discontinuation of study drug might be triggered by an adverse event (AE), a diagnostic or therapeutic procedure, an abnormal assessment (e.g., laboratory abnormalities), or for administrative reasons, in particular withdrawal of the patient’s consent.

If the reason for premature permanent discontinuation of study treatment is an AE, the patient should have a “premature end of study (EOS)” visit with all the assessments performed before the study drug discontinuation, whenever possible. If the patient experiences a life-threatening episode of acute rejection or infection requiring invasive mechanical ventilation or extracorporeal support, the patient will be withdrawn from the study and have the end of study (EOS) visit with all the assessments performed before the study drug discontinuation, whenever possible. If the patient develops a malignancy, the patient will be withdrawn from the study and have the end of study (EOS) visit with all the assessments performed before the study drug discontinuation, whenever possible.

Subjects may prematurely discontinue from the study at any time. Premature discontinuation from the study means that the subject did not undergo an end of study examination as planned per protocol.

Subjects must be withdrawn under the following circumstances:
At their own requestIf the investigator feels it would not be in the best interest of the subject to continueIf the subject violates conditions laid out in the consent form/information sheet or disregards instructions by the study personal

The sponsor has the right to close this study at any time. The IEC and the competent regulatory authority must be informed within 15 days of early termination.

The trial will be terminated prematurely in the following cases:
If adverse events occur which are so serious that the risk-benefit ratio is no longer acceptable.If the number of dropouts is so high that proper completion of the trial cannot realistically be expected.

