### Outcomes {12}

#### Primary endpoint

eGFR calculated by the CKD-EPI formula at 24 months after transplantation

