### Plans to promote participant retention and complete follow-up {18b}

Continuous personal contact with the patients will be established by [name] and our transplant psychologist in order to address possible compliance issue and drop-outs. Based on our preliminary data, a drop-out rate as high as 20% could be expected.

Patients who interrupt the study will undergo the following examinations:
Blood examinations (differential blood count, electrolytes and chemistry, kidney and liver function tests, CRP, LDL, HDL, triglycerides, cholesterol and coagulation status)24 h urinalysisPulmonary function testsECGChest CT scanBronchoscopy with TBB and BALHLA-screeningHistological analysis of TBBMicrobiological analysis of BALBlood CMV count

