## Statistical methods

### Statistical methods for primary and secondary outcomes {20a}

#### Primary endpoint analysis

An *F*-test for the primary endpoint using mixed model analysis will be performed using the function lme from the R package nlme.

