#### Secondary endpoint analysis

Simple ANCOVA analysis for GFR after 12 months and after 24 months, respectively, will be performed.

Chi-square tests, Fisher exact tests, Mann-Whitney *U* tests, or ANOVA will be used to compare differences between the groups. Curves for survival will be generated with Kaplan-Meier method and compared by log-rank tests. A univariate and multivariable Cox regression will be performed to find predictors of survival and CLAD incidence.

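### Life-threatening rejection or infection, and malignancy, end follow-up as well as study drug, so survival, CLAD and month-24 eGFR data are lost for reasons tied to outcome

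*Protocol article*

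**What the plan says.** Section {11b} sets the rule. For a life-threatening episode of rejection or infection it reads: "requiring invasive mechanical ventilation or extracorporeal support, the patient will be withdrawn from the study and have the end of study (EOS) visit". For cancer it reads: "If the patient develops a malignancy, the patient will be withdrawn from the study". In both cases the closing assessments are tied to the end of treatment: "with all the assessments performed before the study drug discontinuation, whenever possible". Permanent discontinuation of study drug for an adverse event leads to a premature end-of-study visit. Subjects must also be withdrawn on other grounds, including when a subject "disregards instructions by the study personal".

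The retention section {18b} adds one list of tests: "Patients who interrupt the study will undergo the following examinations". It names no later visit.

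The endpoints need data beyond that point. The primary endpoint is "eGFR calculated by the CKD-EPI formula at 24 months after transplantation", analysed by an F-test "for the primary endpoint using mixed model analysis will be performed using the function lme from the R package nlme". Secondary endpoints include CLAD, de novo donor-specific antibodies (dnDSA) and survival. For survival, "Curves for survival will be generated with Kaplan-Meier method and compared by log-rank tests".

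Section {20c} limits the modified intention-to-treat set to patients measured at months 0 and 3 and expects no missing data. Sections {14} and {18b} allow for 20% dropout.

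**The concern.** Stopping treatment and ending observation are made one event. A patient who needs ventilation or extracorporeal support for rejection or infection is at high risk of death or graft loss in the following weeks, and observation stops there. Kaplan-Meier and log-rank methods need censoring that is unrelated to prognosis, and censoring at these events is not. CLAD has the same problem, since severe rejection and later CLAD are linked; the Background {6a} itself calls acute cellular rejection a risk factor for CLAD.

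The loss may also differ by arm. The arms receive different immunosuppression, the protocol's own hypothesis is that the new regimen changes rejection and CLAD, and the trial is open-label. If triggers are more frequent in one arm, that arm loses more of its sickest patients, and the survival and CLAD comparison leans in its favour.

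For eGFR the link is weaker. The triggers are not renal events, and values up to withdrawal enter the model. The month-24 value is still missing, and a patient withdrawn before the month-3 measurement drops out of the modified intention-to-treat set altogether.

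**Working it through.** **1. The plan's own figure.** Section {14} goes from 45 to 55 per group for 20% dropout. Dividing, 45 / (1 − 0.20) = 56.25, so 57; multiplying, 45 × 1.20 = 54. The stated 55 lies between the two. It allows for 55 × 0.20 = 11 losses per group and leaves 44. This protects power; it does nothing about bias if the losses depend on outcome.

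**2. What follow-up survives withdrawal.**

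| Endpoint | Needed | Provided after withdrawal |
|---|---|---|
| eGFR | value at month 24 | one closing assessment around drug discontinuation |
| CLAD | follow-up to month 24 | none stated |
| dnDSA | repeated testing | one HLA screen in the closing tests |
| Survival | vital status to month 24 | none stated, apart from the outcome of a reported serious adverse event |
| Rejection | events to month 24 | the triggering episode is already observed; later ones are not |

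**3. Survival illustration.** The documents give no rate for the triggers, so every input here is assumed: share with a trigger, w; share of those who die within 2 months, f = 0.3 to 0.7; other mortality by month 24, m = 5%, independent of the trigger; and no death after withdrawal captured.

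- True 24-month survival = (1 − m)(1 − w·f).
- Kaplan-Meier survival with censoring at withdrawal ≈ 1 − m = 95%, whatever w is.
- True difference, treatment minus control = −(1 − m)·f·(w_T − w_C).

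| w control | w treatment | True difference (percentage points), f = 0.3 to 0.7 | Difference seen |
|---|---|---|---|
| 10% | 20% | −0.95 × f × 0.10 = −2.85 to −6.65 | about 0 |
| 5% | 15% | −2.85 to −6.65 | about 0 |
| 10% | 10% | 0 | about 0 |

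A simulation with 400,000 patients per arm agrees: −2.8 to −6.5 in the first row, −2.9 to −6.6 in the second, and at most 0.1 point seen in any row. In the third row the comparison is unbiased, but survival is overstated in both arms: 95% seen against 0.95 × (1 − 0.10·f) = 92.2% to 88.4% true. Exchanging the arms reverses the sign.

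**4. eGFR illustration.** Let a share w of an arm be withdrawn, and let their month-24 eGFR have been d mL/min below that of the patients who remain. The mean of those remaining then exceeds the whole-arm mean by w × d. With w = 5–20% and d = 5–20 (assumed), this is 0.05 × 5 = 0.25 to 0.20 × 20 = 4 mL/min, against the planned difference of 72 − 60 = 12. This is the error of a simple mean among those remaining in one arm. The error in the treatment difference is w_T·d_T − w_C·d_C, and the mixed model removes the part that earlier eGFR values predict.

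**The case against.** Several points on the other side stand.

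- **Deaths may be captured.** Section {22} records adverse-event outcomes including fatal ones and, where applicable, a follow-up report on a serious event. Section {19} keeps a case report form for patients who do not complete, and section {20c} says follow-up takes place entirely at this centre. A death from the triggering episode therefore has a route into the record. A reader might infer that the article states survival is censored at withdrawal, or that every later death is lost. It says neither; it does not say how such deaths count. The figures in step 3 are therefore an upper bound for those inputs. Partial capture is not neutral either: counting deaths but censoring the survivors of the same episodes also distorts the curve.
- **The triggering rejection has already been observed** and can count as an event.
- **The mixed model does not require leavers to resemble stayers.** It needs missingness at random given the observed eGFR values and model terms, and its contrast uses the whole curve.
- **Premature-visit eGFR.** The timeline names the outcome eGFR at EOS, so a reader might infer that a value from a premature visit can replace month 24. The timeline's EOS column is 24 months, the endpoint is fixed at 24 months, and the model indexes values by planned time point. The documents do not support the substitution.
- **Withdrawal for disregarding instructions** is not triggered by outcome. It shows only that leaving treatment and leaving the study are joined.
- **The article condenses a fuller protocol**, which may provide for vital status after withdrawal. That lowers certainty that all follow-up ends, but it does not change the explicit wording. An analysis plan cannot recover data that were never collected.

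**Conclusion.** The concern holds for follow-up after withdrawal. As written, the rule takes patients out of the study at events that strongly predict death and graft failure, and the article provides no later eGFR, CLAD, dnDSA or vital-status collection. Censoring there is informative for survival and CLAD. For the primary endpoint the month-24 value is lost, and the analysis then rests on missingness at random given observed eGFR.

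Neither the size nor the direction of the bias can be fixed from the documents. Under the assumptions shown, a true survival difference of about 3 to 7 percentage points could appear as none, and the mean eGFR of those remaining in an arm could be 0.25 to 4 mL/min too high. If triggers are equally frequent and equally severe in both arms, the comparison is unaffected and only the level of survival is overstated.

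A reader might be tempted to multiply the 12 mL/min target by the 20% dropout allowance and call the result the bias. That would assign all dropout to these triggers in one arm and assume complete loss of benefit. The documents support neither, and patients who die have no month-24 eGFR under any follow-up rule.

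**What to change.** Leave the rules for stopping study drug as they are; this point takes no view on them. Separate the end of study treatment from the end of follow-up:

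- In section {11b}, replace the wording that removes the patient from the study with a statement that the patient remains in follow-up.
- For every randomised patient, collect eGFR at the planned time points, rejection, CLAD, dnDSA and vital status to month 24, unless the patient withdraws consent to data collection.
- Analyse these patients in the arm to which they were randomised.
- Reconcile section {20c}, which expects no missing data, with the 20% dropout in sections {14} and {18b}.

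The cost is a protocol amendment and some continued data entry. Follow-up already takes place at this one centre, so little or no new visit burden is expected. The downside is small: the estimated effect will include time off study treatment and may be somewhat smaller.
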